### Dissemination policy

The results of the study will be communicated by the research team to the local organizations who participated in the study, the professional sponsors who are involved in healthy ageing and also the public (e.g., via the websites of the retirement fund and other operational partners). The study will result in several publications in peer-reviewed journals.

## Discussion

The ALAPAGE study is a pragmatic cRCT which aims at assessing the effectiveness, process, and cost effectiveness of a combined diet and physical activity collective intervention among older French people who live at home. It is conducted by a multidisciplinary research team (epidemiology/public health, human nutrition, physical activity, health economics, social psychology) in close partnership with experienced operational partners in health promotion among elders.

This study has several strengths. First, the ALAPAGE program on diet and physical activity evaluated in this study is based on “real-life” interventions, i.e., collective prevention workshops that have been implemented by our operational partners for many years. Based on a diagnostic study, we optimized these workshops and tools using both a participatory approach involving dieticians, APA professionals and elderly people, and a theory-based approach [48, 49]. This development process is recommended to enhance the interventions’ fidelity, suitability to context, and effectiveness [67]. Secondly, this study includes an innovative active recruitment strategy to improve participation of hard-to-reach (i.e., socioeconomically-disadvantaged and socially-isolated) older people. It will thus contribute to creating greater equity in healthy ageing [5] and help prove the effectiveness of strategies aimed at identifying socially isolated/lonely people and also connect them to services [15]. Third, this cRCT includes a wide range of outcomes relating to eating behaviors, physical activity and fitness but also to social aspects like quality of life and feelings of loneliness. The methodology will also allow us to explore the causal mechanisms of the intervention and to understand how the ALAPAGE program – if effective, as we hypothesize -- improves the behaviors of participants [67].

We must also acknowledge some limitations. First, the recruitment of participants will take place after the randomization of workshops. This may lead to recruitment bias and a discrepancy in the characteristics of the participants in both the intervention and the control groups [68]. As part of this pragmatic cRCT, our operational partners did not find it feasible to recruit participants before the cluster randomization or by means of a blinded and independent person. To limit recruitment bias (e.g., participants in the intervention group are more interested in diet and physical activity issues and are thus more likely to change their behaviors than those in the control group), we will use a waiting-list control group design. Consequently, all participants are interested in participating in workshops on diet and physical activity. Second, due to feasibility constraints, the times points differ slightly between the intervention and control groups for some of the outcomes. However, we have done our best to limit these differences and to reconcile methodology requirements and practical feasibility. We hypothesize that this will have a limited impact on our results. Lastly, we cannot exclude differing attrition rates between the intervention and control groups that may lead to biased estimates of the intervention’s effects. In this instance, we plan to use appropriate econometric techniques (e.g., a Heckman sample selection correction model [69]) to correct for attrition bias [70].

The results of this study should help to implement public health interventions that are effective at improving dietary diversity, physical activity and fitness, and social outcomes among older people who live at home. They will contribute to the improvement of healthy aging while limiting social inequalities. The ALAPAGE program has been developed and will be evaluated in close relationship with major operational partners of healthy aging in France, thus providing a unique opportunity to expand its reach.

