Staff from local organizations --for (1)--, or social workers --for (2)--, relay information about the study both orally and in writing and prescreen participants for eligibility criteria. During the inclusion session/visit (S0 and V0 for the intervention and control groups respectively, see Fig. 1), the dietician reads the written information aloud to the participants, verifies eligibility criteria and asks for informed consent in writing.

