***Secondary outcomes process evaluation***											
Fidelity, dose, reach of the intervention (attendance lists, information sheets completed by the local organizations, dieticians and APA professionals after each session)	I	X	X	X	X	X	X	X			
Fidelity, dose of the intervention (questionnaire on self-reported exercises in daily activities, participation in post-session activities between participants)	I							X			X
Mechanisms of the intervention (questionnaire on beliefs, attitudes, intention towards physical activity)	I			X				X			X

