### Data collection procedure

Data collection is performed on the premises of local organizations under the supervision of a dietician and/or an APA professional, except for: one 24-hour recall performed at home during week 5 for the control group and during week 18 for both groups; and the number of steps during 1 week recorded at home three times for each group (Table 2).

Face-to-face interviews with participants are performed by researchers, who have significant qualitative research experience, in the month following T2 at the local organization or at home depending on the participants’ preference.

All study participants will be financially compensated (the intervention group will receive a 15 € voucher; the control group will receive two 15 € vouchers, the second voucher compensating for the additional participation in the measurement visit).

Expected and non-expected serious adverse events and other unintended effects of the intervention (i.e., those that require hospitalization, result in a significant or long-lasting disease/disability, or death) are collected and immediately reported to the research team by the sessions’ dieticians and APA professionals.

Prior to the commencement of the study, dieticians and APA professionals participate in training sessions that are led by research team members (including by one person who is certified in Good Clinical Practices [GCP]) and includes (i) a two-hour video conference that presents the study and its data circuit; (ii) a half-day session on research issues (e.g., clinical practices, information, consent, notification of adverse events); and a further one and a half day session on the study’s content and visits (e.g., program, objectives, tools).

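### Recruitment follows allocation and the waiting list only partly limits selection; adjusting for baseline only after an observed imbalance, apparently as a main effect, is too weak a safeguard for the group-by-time contrast.

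*Protocol article*

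**What the plan says.** **Order of events.** The Discussion lists as its first limitation that "the recruitment of participants will take place after the randomization of workshops". It adds that the operational partners "did not find it feasible to recruit participants before the cluster randomization or by means of a blinded and independent person". Under Recruitment of participants, host staff (usual route) or social workers (active route) "relay information about the study both orally and in writing and prescreen participants for eligibility criteria". Eligibility is verified and consent taken later, "During the inclusion session/visit (S0 and V0 for the intervention and control groups respectively", that is, at a session that already belongs to one arm.

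**The remedy offered.** To limit the bias, the authors write, "we will use a waiting-list control group design". They continue: "Consequently, all participants are interested in participating in workshops on diet and physical activity".

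**What each arm is offered.** The intervention arm starts its weekly sessions at once. The control arm attends measurement visits and receives the programme only after the study, which lasts 19 weeks per participant (Study design and setting; Control group). Compensation also differs: one voucher in the intervention arm, while "the control group will receive two 15 € vouchers" (Data collection procedure).

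**The analysis.** Data analysis specifies mixed models with time, group and their interaction as fixed factors. It plans a between-group comparison of baseline characteristics, and brings baseline values in as covariates only where the groups turn out to be imbalanced. Additional file 7, cited for model detail, is not shown.

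**The concern.** The bias the authors name is that people entering intervention workshops may be more inclined to change. A waiting list ensures that everyone wants the programme in principle. It does not ensure that those who agree to wait are as ready to change as those who agree to start now, so the step from the waiting list to comparable groups does not follow.

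This kind of selection acts on the T0-T2 change itself, and that change is what the group-by-time term estimates for dietary diversity and for the chair stand test. A difference in level at baseline drops out of that term; a difference in propensity to improve does not. The analysis therefore has to carry some of the load, and its stated rule has two weaknesses: it waits for an imbalance to show itself, and as written it adds covariates without a time interaction.

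**Working it through.** **1. The plan's own figure, and the standard error used below.** Inputs from Sample size calculation: 300 and 150 participants in 30 and 15 workshops of 10, ICC 0.03, 30% dropout, α = 0.05 (two-sided assumed).

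- Analysed per workshop: 10 × 0.7 = 7. Design effect: 1 + (7 − 1) × 0.03 = 1.18.
- Effective control size: 150 × 0.7 / 1.18 = 89.0; intervention: 178.0.
- SE of the contrast, with its SD set to 1: √(1/89.0 + 1/178.0) = 0.130.
- Effect detectable with 95% power: (1.960 + 1.645) × 0.130 = 0.47 SD. At the planned 1 SD for dietary diversity, power exceeds 99.9%.

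The stated 95% is thus a floor for dietary diversity. The article gives no effect size for the chair stand, so the figure is neither confirmed nor refuted there.

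**2. Why a main effect does not help.** Let G be group, t time (0 or 1) and X a baseline covariate.

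- Model with a main effect: E(Y) = b0 + b1·G + b2·t + b3·G·t + c·X.
- Change from t = 0 to t = 1: b2 + b3·G. The term c·X cancels.
- If people with X = 1 improve by δ more, and the share with X = 1 is p1 in the intervention arm and p0 in control, the estimate of b3 is shifted by δ(p1 − p0), whether or not c·X is in the model.
- With a term d·X·t the change becomes b2 + b3·G + d·X, and X can absorb the shift.

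Simulation: 45 workshops of 10, two time points, no true programme effect, p1 − p0 = 0.30, δ = 0.5 SD (both assumed), 60 replicates per row, so the averages carry some simulation error.

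| Data | No covariate | Main effect only | Covariate × time |
|---|---|---|---|
| Complete | 0.149 | 0.149 | −0.004 |
| 30% random dropout | 0.130 | 0.131 | −0.017 |

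**3. How often the conditional rule would be triggered.** At baseline with 10 per workshop, the design effect is 1 + 9 × 0.03 = 1.27, and SE = √(1.27 × (1/300 + 1/150)) = 0.113. Chance that a 5% test flags a true shift in a measured variable:

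| Shift | Test allowing for clustering | Test ignoring clustering |
|---|---|---|
| 0.1 SD | 14% | 20% |
| 0.2 SD | 43% | 51% |
| 0.3 SD | 76% | 82% |

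The baseline tests named in the article take no account of clustering. They flag more often, but also raise more false alarms. Either way a 0.2 SD shift is missed about half the time.

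**4. Illustrative size.** Bias = difference in share × difference in change. Neither factor is in the documents. With 10 to 30 percentage points and 0.25 to 0.5 SD: from 0.10 × 0.25 = 0.025 SD to 0.30 × 0.5 = 0.15 SD. The false-positive rate is P(|Z + bias/0.130| > 1.96): about 5% at 0.025 SD, 9% at 0.075 SD and 21% at 0.15 SD.

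**The case against.** The limitation is disclosed. The Discussion names recruitment bias, describes the motivation mechanism, explains why earlier or blinded recruitment was not possible, and claims only to limit the bias. That is fair: the quarrel is with one inference and with the adjustment rule, not with candour.

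The magnitudes are assumed, and nothing in the documents shows that ready-to-change people decline the control offer. Even the top of the range, 0.15 SD, is 15% of the planned 1 SD effect on dietary diversity. This stands, although 0.15/0.47 is about a third of the effect that the design detects with 95% power. The listed covariates do not measure readiness directly, so adjustment recovers only what they carry. This also stands. Additional file 7 may specify the covariate terms more fully; the conditional rule itself, however, is in the article.

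Three stronger readings are tempting and are not supported:

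- **That selection can be neither seen nor corrected.** Data analysis compares measured baseline characteristics between arms and allows adjustment, and Sample characterization lists useful covariates.
- **That the share recruited through the active strategy cannot be compared by arm.** Type of recruitment is a planned moderator, which requires the route of enrolled participants in both arms.
- **That Table 2 shows no recruitment log in control workshops.** The intervention-only row, "Fidelity, dose, reach of the intervention (attendance lists, information sheets completed by the local organizations, dieticians and APA professionals after each session", measures delivery of the programme. It is not a record of refusals, and a screening log may sit in the full protocol.

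**Conclusion.** The point holds as a modest weakness in the analysis rule and one overstated inference. Enrolment after allocation by unblinded staff is stated outright. That participants know their arm when they consent is a strong inference from the arm-specific inclusion visits. The waiting list makes all participants interested, but not necessarily equally ready to change.

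Conditional adjustment would miss a 0.2 SD shift about half the time. A covariate main effect leaves the group-by-time estimate essentially unchanged, exactly so with complete data. Measured imbalance can be seen and, with the right model terms, partly corrected. Selection on unmeasured motivation cannot; in Table 2 the questionnaire on beliefs, attitudes and intention is scheduled for the intervention group only and concerns physical activity only.

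The 0.025 to 0.15 SD range shows what such selection could do under the assumptions stated. It is not an estimate of bias in this trial: the low end is negligible, the high end is not.

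**What to change.** 1. In Data analysis, replace the conditional rule with a fixed, prespecified set of baseline covariates that the trial already collects: recruitment route, age, sex, perceived financial situation and physical activity history. Include them in both primary models whatever the observed balance. Give each a covariate-by-time term, or model T2 given T0 and these covariates, so that they act on the change contrast.
2. In the Discussion, say that the waiting list only partly limits recruitment bias, and that residual selection on motivation remains and cannot be removed by adjustment.

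No new data are needed. The cost is a few degrees of freedom, small against an expected 450 × 0.7 = 315 participants with T2 data in 45 workshops. The limit is that these covariates stand in for readiness only indirectly, so the change reduces the exposure without removing it.

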### Roles and responsibilities

The steering committee for the ALAPAGE study is comprised of the study’s scientific coordinator, the principal investigator (and representative of the study’s sponsor) and several of his team members who are responsible for the project’s management, representatives from operational partners (Carsat Sud-Est, ASEPT PACA, Mutualité Française Sud, Géront’ONord, SudEval and Trophis), and a number of representatives from the scientific committee. The steering committee meets regularly depending on the research’s needs, including reviewing the study’s progress and providing overall feedback to each of its members. It is also responsible for making any important decisions regarding the proper conduct of the study and compliance with the protocol. It verifies ethical compliance.

Finally, a scientific committee composed of experts in health psychology, nutritional epidemiology, adapted physical activity and health economics meet at least once a year (or more times if necessary) to validate methodological aspects of the study, provide guidance on the study’s conduct and the dissemination of results.

## Data Availability

Not applicable.

## Abbreviations

APA: Adapted physical activity
cRCT: cluster randomized controlled trials
DAS: Diversity ALAPAGE Score
FFQ: Food Frequency Questionnaire
GCP: Good Clinical Practices
LiFE: Lifestyle-integrated Functional Exercise program
QALYs: Quality Adjusted Life Years
